## Abstract

**Background:**

The morbidity of pancreatic resection remains high, with pancreatic fistula being the most common cause. The important question is whether any postoperative treatment adjustment may prevent the development of clinically significant postoperative pancreatic fistulae. Recent studies have shown that intraabdominal drains and manipulation using them are of great importance. Although authors of a few retrospective reports have described good results of pancreatic resection without the use of intraabdominal drains, a recent prospective randomized trial showed that routine elimination of drains in pancreaticoduodenectomy is associated with poor outcome. An important issue arises as to which type of drain is most suitable for pancreatic resection. Two types of surgical drains exist: open drains and closed drains. Open drains are considered obsolete nowadays because of frequent retrograde infection. Closed drains include two types: passive gravity drains and closed-suction drains. Closed-suction drains are more effective, as they remove fluid from the abdominal cavity under light pressure. However, some surgeons believe that closed-suction drains represent a potential hazard to patients and that negative pressure might increase the risk of pancreatic fistulae. Nobody has yet specifically dealt with the question of which kind of drainage is most appropriate in pancreatic surgery.

**Methods/Design:**

The aim of the DRAins in PAncreatic surgery (DRAPA) trial is to compare the closed-suction drain versus the closed passive gravity drain in pancreatic resection. DRAPA is a dual-centre, prospective, randomized controlled trial. The primary endpoint is the rate of postoperative pancreatic fistula; the secondary endpoint is postoperative morbidity with follow-up of 3 months.

**Discussion:**

No study to date has compared different types of drains in pancreatic surgery. This study is designed to answer the question whether any particular type of drain might lower the rate of postoperative pancreatic fistula or other complications.

**Trial registration:**

ClinicalTrials.gov Identifier: NCT01988519. Registered 13 November 2013.

## Background

Pancreatic resection is the only potentially curative method for treatment of pancreatic neoplasms. These surgical procedures are technically demanding, with pancreaticoduodenectomy and distal pancreatectomy being the most common [1]. Although the mortality rate associated with these procedures has dropped to under 5% in recent decades, the morbidity remains high [2,3]. The most significant and ominous complication is the postoperative pancreatic fistula (POPF) [4]. Although this complication is in most cases not life-threatening, it prolongs the hospital stay and requires additional treatment (for example with antibiotics, nutritional support) and interventions (such as endoscopy, interventional radiology and/or reoperation) and thus increases the cost of the treatment [2,5]. According to the International Study Group of Pancreatic Fistula (ISGPF) consensus definition, pancreatic fistula is diagnosed if the amylase content in fluid from the intraabdominal drains exceeds three times the normal serum concentration [6].

Several methods have been studied in the past with the goal of lowering the pancreatic fistula rate. They include pharmacological prophylaxis with octreotide [7] and various technical modifications of pancreatic remnant management after pancreaticoduodenectomy [8,9] and after distal pancreatectomy [10]. However, the use of octreotide remains controversial, and none of the studied techniques proved to be superior.

Another method of influencing the rate of pancreatic fistulae and postoperative complications is the use of intraabdominal drains and manipulation with them. Recent studies show that the use of drains, the type of drain and the manipulation with the drain can lower the pancreatic fistula rate [11-13].

Intraabdominal drains have traditionally been used in surgical fields [14]. The main significance of the drains is to prevent formation of intraabdominal fluid collection; furthermore, it helps with early diagnosis of postoperative bleeding, pancreatic and biliary leak, or anastomotic dehiscence [15-17]. In some cases, keeping the drain in place for a longer period of time can be part of conservative treatment of the pancreatic fistula, such as by creating a controlled pancreaticocutaneous fistula until the fistula has healed spontaneously without any additional treatment [11,18].

Recent studies show that the use of drains might not be beneficial for the patient, such as in cholecystectomy, appendicectomy, gastric resection, bowel resection and liver resection [19]. Moreover, the use of drains might even be harmful for the patient, as it can slow down recovery and the restoration of bowel movements and can prolong the hospital stay or even cause postoperative complications such as retrograde intraabdominal infection, hollow organ perforation and/or loss of fluid and electrolytes.

Pancreatic surgery is different from surgery of hollow organs. Unlike enteric anastomotic dehiscence, which often presents with pneumoperitoneum and frequently causes peritonitis [20], pancreatic leak is more frequent, but the clinical course is not usually so dramatic [4]. Pancreatic leak or pancreatic fistulae can be easily diagnosed by analysing the amylase concentration in the drain effluent [21]. However, the amylase concentration is increased in the majority of patients on the first postoperative day, even in those patients who do not develop pancreatic fistulae in the postoperative course. This means that the pancreatic anastomosis is not ‘watertight’ in the majority of the patients [22].

The important question is whether any treatment adjustment in the postoperative course may prevent the development of clinically significant POPF. Recent studies have shown that intraabdominal drains and the manipulation with them are of great importance [11,13,23]. Three important questions arise when studying drains in pancreatic surgery:Is it necessary to use drains following pancreatic resection?When should the drains be removed?Which type of intraabdominal drain is most suitable?

These questions are addressed in turn in the subsections below.

### Is it necessary to use drains following pancreatic resection?

Drains have traditionally been used in abdominal surgery in most procedures, including pancreatic resection. The first pilot study describing the results of pancreaticoduodenectomy in 22 patients without drains was published in 1992 [24]. A number of retrospective cohort studies have shown superior results of pancreatic resection without routine intraabdominal drainage [13], but only two randomized studies compared pancreatic resection with versus without drains. The first randomized controlled trial was conducted in Memorial Sloan Kettering Cancer Center in New York City [14]. It failed to show that surgically placed intraabdominal drains reduce the rate of complications.

In a recent study, Van Buren *et al*. showed level I evidence that elimination of routine drainage in all cases of pancreaticoduodenectomy results in unacceptably poor outcomes, and thus this approach cannot be recommended [25]. Further studies are needed to confirm these results.

### When should the drains be removed?

Two studies have addressed this question. In one retrospective study, researchers compared removal of the drains on day 4 versus day 8 [26]; in the other, investigators in a prospective randomized trial compared removal of drains on day 3 versus after day 5 in patients with low risk of POPF [15]. Both studies showed a lower rate of intraabdominal complications and fluid collections, and a lower rate of POPF, in the group with early drain removal.

### Which type of intraabdominal drain is most suitable?

The final issue regarding drains in pancreatic surgery is which type of drain to use. Two types of surgical drains exist: open drains and closed drains. Open drains are considered obsolete because their use is associated with frequent retrograde infection [27]. Closed drains include two types: passive gravity drains and closed-suction drains. Generally speaking, closed-suction drains are preferred in the United States [28,29], and passive gravity drains are used more frequently in Europe [30]. Only two studies have compared the different types of drains: the Penrose drain versus closed-suction drain [31,32]. However, these two studies were retrospective and conducted over a long period of time (17 years and 22 years, respectively); comparison of the drains was not the primary endpoint; and the studies’ results are contradictory. Nobody has specifically dealt with the question of which kind of drainage is more appropriate in pancreatic surgery [12]. Diener *et al*., in a systematic review of the current state of evidence for drains in pancreatic surgery, stated that the role of different types of drains remains unclear [11].

## Methods/Design

### Objectives and hypothesis

The aim of the DRAins in PAncreatic surgery (DRAPA) trial is to compare two types of intraabdominal drains in pancreatic resection and their effect on the development of POPF and postoperative complications. Closed-suction drains are more effective, as they remove fluid from the abdominal cavity under light negative pressure [13]. However, some surgeons believe that closed-suction drains represent a potential hazard to patients [33] and that negative pressure might increase the risk of POPF [13].

The following hypotheses will be tested:H0: The risk of development of POPF and postoperative complications is equal in both groups.H1: The risk of development of POPF and postoperative complications is different between the groups.

### Study population and eligibility criteria

The DRAPA trial will encompass two participating centres: University Hospital Hradec Králové and University Hospital Olomouc, both in the Czech Republic. All patients who are scheduled for pancreatic resection at the two participating centres will be screened and assessed for eligibility.

Only patients who undergo pancreaticoduodenectomy or distal pancreatic resection will be included in the study. Patients with nonstandard procedures or a procedure associated with higher morbidity will be excluded from the study to achieve a homogeneous study group. Detailed inclusion and exclusion criteria are described below.

#### Inclusion criteria

Patients scheduled for primary pancreaticoduodenectomy or distal pancreatic resection in participating centresAged 18 years or olderSigned informed consent provided

#### Exclusion criteria

No pancreatic resection performed: nonresectable tumourTotal pancreatectomy, central pancreatectomy or enucleationMultivisceral resectionLaparoscopic procedureResection of the portal vein and reconstruction with a graftLack of compliance, informed consent not provided or refusal to participate

### Sample size calculation

The sample size calculation is based on the expected rate of POPF from our previous experience, as there exist no pilot data comparing the closed-suction drain and closed passive gravity drain in pancreatic surgery. The POPF rate in the closed passive gravity drain group is expected to be 35% based on previous studies [2,3]. The POPF rate in the closed-suction drain group is expected to drop to half that rate (17.5%). The sample size calculation is based on a one-sided *t*-test for differences with respect to the primary endpoint, which is the POPF rate. With α= 5% and β = 20%, a sample size of 97 patients per group is necessary to detect a difference between the groups. With an expected dropout rate of 15%, we plan to enrol 223 patients into the study.

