## Discussion

Despite growing evidence in favour of pancreatic resection without intraabdominal drainage [13], routine elimination of drains cannot be recommended [25]. Rather more, drains could diminish the rate and severity of POPF in patients with high risk of POPF. Drains could possibly be avoided in patients with low risk of POPF [46]. However, the majority of pancreatic surgeons still consider routine placement of intraabdominal drains mandatory [15-17]. Once a decision is made to use intraabdominal drains, a controversy remains about which type of drain is most suitable in pancreatic resection [47]. Two types of drains are commonly used nowadays: passive gravity drains [26,30] and closed-suction drains [28,29]. Closed-suction drains are more effective, as they remove fluid from the abdominal cavity under light negative pressure [13]. However, some surgeons believe that closed-suction drains represent a potential hazard to patients [33] and that negative pressure might increase the risk of POPF [13]. No study conducted to date has specifically addressed the question of which type of drain is most beneficial for patients [12,13].

The DRAPA trial is designed to compare closed-suction drains with passive gravity drains in pancreatic surgery. Using the ISGPF definition of POPF will allow us to compare the results of this trial with those of other trials of drains in pancreatic surgery. This trial can show whether closed-suction drains represent hazards to patients or are beneficial in terms of decreasing POPF rates.

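### The 97 patients per group are labelled as a one-sided 5% calculation but match a two-sided 5% one; the label, not the size, is wrong and conflicts with the non-directional hypothesis

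*Protocol article*

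**What the plan says.** All references are to the protocol article.

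- **Sample size calculation.** The basis is given as: "The sample size calculation is based on a one-sided *t*-test for differences with respect to the primary endpoint". The control assumption is: "The POPF rate in the closed passive gravity drain group is expected to be 35% based on previous studies". The closed-suction rate is taken as half of that, 17.5%. The result is: "With α= 5% and β = 20%, a sample size of 97 patients per group is necessary to detect a difference between the groups".
- **Objectives and hypothesis.** The null is equal risk in both groups. The alternative has no direction: "H1: The risk of development of POPF and postoperative complications is different between the groups". The same section reports the view that negative pressure might raise the POPF risk.
- **Statistical methods.** The equality null is repeated, POPF is compared by adjusted binary logistic regression, and the threshold is P < 0.05 without a one-sided qualifier. Two-tailed testing is written out only for the t-tests on continuous secondary endpoints.
- **Discussion.** Both directions are of interest: "This trial can show whether closed-suction drains represent hazards to patients or are beneficial in terms of decreasing POPF rates".

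**The concern.** The stated basis and the stated result of the sample size do not belong together. A reader who enters the published inputs with a one-sided 5% test obtains a clearly smaller number than 97. The label also clashes with the hypothesis, because a one-sided test directed at a reduction cannot deliver a finding of hazard.

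At stake is the decision rule for the primary endpoint. The sample size section carries the only explicit word on sidedness attached to the POPF comparison, and that word is *one-sided*. The hypothesis and the unqualified P < 0.05 imply the opposite. A result favouring suction with a two-sided P between 0.05 and 0.10 would count as significant under one reading and not under the other. Treating staff know the allocation, so this should be settled before results are seen.

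**Working it through.** **Inputs (Sample size calculation):** p1 = 0.35, p2 = 0.175, difference d = 0.175, α = 0.05, power 0.80, equal groups.

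**Constants:** z(power) = 0.8416; z(α) = 1.6449 one-sided and 1.9600 two-sided. The squared sums are (1.6449 + 0.8416)² = 6.183 and (1.9600 + 0.8416)² = 7.849. The variance sum is 0.35 × 0.65 + 0.175 × 0.825 = 0.2275 + 0.144375 = 0.371875, and d² = 0.030625.

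**1. Reproducing 97.**

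- t-test with unpooled variance: SD = √(0.371875 / 2) = 0.4312. Solving for 80% power gives 96.3 two-sided (rounds up to 97) and 75.8 one-sided (76).
- Arcsine: h = 2·asin√0.35 − 2·asin√0.175 = 0.4029, n = 2 × (squared sum) / h². Two-sided 2 × 7.849 / 0.1623 = 96.7 (97); one-sided 2 × 6.183 / 0.1623 = 76.2 (77).
- Normal, unpooled: n = 0.371875 × (squared sum) / 0.030625. Two-sided 95.3 (96); one-sided 75.1 (76).
- Normal, pooled variance under the null: p̄ = 0.2625, n = [z(α)·√(2 × 0.2625 × 0.7375) + z(power)·√0.371875]² / 0.030625. Two-sided 98.0 (99); one-sided 77.1 (78).

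**2. Could a more conservative one-sided method give 97?**

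| Method | One-sided 5% | Two-sided 5% |
|---|---|---|
| t-test, unpooled SD 0.4312 | 76 | **97** |
| Arcsine | 77 | **97** |
| Normal, unpooled | 76 | 96 |
| Normal, pooled | 78 | 99 |
| t-test, pooled SD 0.4400 | 79 | 101 |
| Fisher exact | about 87 | 108–109 |
| Pooled, continuity-corrected | 89 | 110 |
| t-test, control-arm SD 0.4770 in both arms | 93 | 118 |

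A one-sided calculation with a worst-case SD of 0.5 overshoots, at 101 to 102, and does not use the stated rates for the variance. None of the one-sided methods tried gives 97; two standard two-sided methods do.

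**3. Power at 97 per group.**

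- Unpooled: the standard error is √(0.371875 / 97) = 0.0619, and 0.175 / 0.0619 = 2.826. Two-sided Φ(2.826 − 1.960) = 80.7%; one-sided Φ(2.826 − 1.645) = 88.1%.
- Pooled: 79.6% two-sided and 87.5% one-sided.

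The stated β of 20% thus also fits only the two-sided reading.

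**4. What the label would change if followed.** With 97 per group and an overall POPF rate of 26.25%, the standard error under the null is √(2 × 0.2625 × 0.7375 / 97) = 0.0632. In an unadjusted comparison, significance in favour of suction needs an observed drop of 1.960 × 0.0632 = 12.4 percentage points two-sided, or 1.645 × 0.0632 = 10.4 points one-sided. The false-positive rate in that direction is 2.5% against 5%. A one-sided test for a reduction has no rejection region for harm.

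**The case against.** The strongest reply is that the rest of the article already settles the matter. The alternative hypothesis names POPF and is non-directional. Statistical methods, which governs the analysis, repeats the equality null, names a logistic regression and uses P < 0.05 without a one-sided qualifier. An analyst would take the test from there; one who copied the sample size paragraph literally would also have to run a t-test on a binary endpoint, contrary to the analysis section. The trial has about 80% power for the two-sided test, so no patient is missing.

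Much of this stands, and it rules out several stronger readings:

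- *A reader might infer that the trial is wrongly sized.* It is not: 97 per group suits the two-sided test that the hypothesis implies.
- *A reader might infer that a one-sided primary analysis is planned, or that the sample size section alone bears on sidedness.* The hypothesis and the unqualified threshold also bear on it and point to two-sided. The 5% error rate and the loss of any harm conclusion are therefore conditional on someone taking the rule from the sample size section.
- *A reader might blame the t-test for a binary endpoint.* As a sizing approximation it does no damage here: run two-sided with unpooled variance, it gives 97.
- *A reader might count the unstated sidedness of the logistic regression as an omission.* An article may leave that to the full protocol or analysis plan, so it is no finding in itself.

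The match to 97 also depends on the formula, since two-sided methods range from 96 to 118. That weakens any claim about which method was used, but does not rescue the one-sided label. The explicit statement remains wrong, and an analysis plan not shown would not correct it.

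**Conclusion.** The point holds as an error of description. At the stated rates, α and power, a one-sided test needs about 76 to 79 per group (89 to 93 under conservative variants), whereas 97 is the two-sided 5% result by t-test with unpooled variance or by arcsine. Power at 97 is about 80% two-sided and about 87 to 88% one-sided.

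The label contradicts both its own figure and the non-directional hypothesis. It leaves an explicit one-sided statement for the primary endpoint standing against an implied two-sided one. The size of the trial is not in question.

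The conclusion assumes equal allocation and an unadjusted comparison for sizing, and takes α = 5% as written. A one-sided α of 2.5% would give the same number, but that is not what the text says. The direction of the one-sided test is taken from the expected drop with suction.

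**What to change.** In Sample size calculation, replace *one-sided* with *two-sided*. Optionally name a two-proportion method that reproduces the figure, for example: two-sided comparison of two proportions by the arcsine method, 35% versus 17.5%, α = 5% two-sided, power 80%, 97 patients per group. A general reference to a normal approximation should be avoided, because those formulas give 96 or 99.

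In Statistical methods, add that the treatment effect on POPF in the primary logistic regression is tested two-sided at 0.05.

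The cost is two sentences. The 97 per group do not change, and this correction adds no patients. It should be made before any comparison by group is run.

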### Methods for avoiding bias

#### Minimizing systemic bias

Patients will be randomized to one of the drain groups during the surgical procedure after resectability of the tumour is confirmed. Randomization will be accomplished using balanced permutation blocks by generation of random numbers in order to obtain homogeneity between groups. Patients scheduled for pancreaticoduodenectomy and distal pancreatectomy will be randomized separately, as these two procedures are different with regard to the course and consequences of POPF [25,44]. Opaque, sealed envelopes will be produced, labelled with the randomization number and containing a sheet that states the group allocation for the patient. Randomization envelopes will be used in consecutive order. Basic characteristics of the patient and the day of randomization will be documented on a data sheet so that compliance to the randomization scheme may be checked retrospectively. If patients are excluded from the study after randomization, their numbers will not be reused. Obviously, operating surgeons, attending physicians and nursing staff cannot be blinded, as the drains look different. However, outcome assessors will be blinded. The randomization process will follow the CONSORT guidelines (Figure 1) [45].

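### The planned enrolment of 223 covers about 13% dropout, not the stated 15%, if 97 patients per group are to remain; the effect on power is about one point or less

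*Protocol article*

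**What the plan says.** The protocol article's section on sample size calculation gives three linked figures. It states that "a sample size of 97 patients per group is necessary to detect a difference between the groups", which is 194 patients in total. It expects 15% dropout. It then concludes: "With an expected dropout rate of 15%, we plan to enrol 223 patients into the study".

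The other inputs in the section are a fistula (POPF) rate of 35% with passive gravity drains, half of that (17.5%) with closed-suction drains, α of 5% and β of 20%. On the test it says "The sample size calculation is based on a one-sided" *t*-test. No inflation formula is given, and no other section gives a different enrolment figure.

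Under minimizing systemic bias, the article places randomization during surgery and foresees losses after it: "If patients are excluded from the study after randomization, their numbers will not be reused". It describes no replacement of such patients.

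**The concern.** A dropout rate is ordinarily a fraction of those enrolled. To keep a required number after dropout, that number is divided by one minus the rate. The enrolment figure here looks as if the required number was instead increased by 15%. That gives a smaller total, because 15% of 223 is more than 15% of 194.

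At stake is whether the trial's recruitment target delivers the group size that the same paragraph calls necessary. A reader of the section would take it that a 15% loss is covered.

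**Working it through.** **Inputs, all from the sample size section:** 97 per group; dropout 15%; enrolment 223; POPF rates 0.35 and 0.175; α = 0.05. Equal allocation is implied by the single per-group figure and the balanced blocks.

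**1. Reproducing 223.**
- Required total: 2 × 97 = 194.
- 194 × 1.15 = 223.1, which rounds to the stated 223.

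The match is close, but the multiplication is inferred, since the article does not show its method.

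**2. Taking the plan's figures forward.**
- 223 × (1 − 0.15) = 189.55 patients, or 94.8 per group.
- Shortfall: 194 − 189.55 = 4.45, that is 4 to 5 patients, or about 2 per group.
- Dropout that 223 does cover: 1 − 194/223 = 29/223 = 13.0%.

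This step does not depend on how 223 was obtained.

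**3. Enrolment that keeps 194 after 15% dropout.**
- 194/0.85 = 228.2, so 229, or 230 for equal groups.
- Difference from 223: 6 to 7 patients. For 229 this is 6/223 = 2.7%.

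**4. Effect on power.** Normal approximation with pooled variance under the null hypothesis:

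power = Φ{ [d − z·√(2p̄(1 − p̄)/n)] / √[(p₁(1 − p₁) + p₂(1 − p₂))/n] }

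Here d = 0.35 − 0.175 = 0.175, p̄ = 0.2625, 2p̄(1 − p̄) = 0.3872, and p₁(1 − p₁) + p₂(1 − p₂) = 0.2275 + 0.1444 = 0.3719.

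| Test | n = 97 per group | n = 94.8 per group | Loss (points) |
|---|---|---|---|
| One-sided 5% (as written) | 87.5% | 86.8% | 0.7 |
| Two-sided 5% | 79.6% | 78.6% | 0.9 |

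Losses are taken before rounding (0.8745 − 0.8677 and 0.7957 − 0.7864).

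A *t*-test calculation with the unpooled variance gives a similar picture:
- One-sided: 87.9% at 97 per group, 87.0% at 94 and 87.3% at 95.
- Two-sided: 80.3% at 97 per group, 79.0% at 94 and 79.5% at 95.

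The one-sided Fisher exact test, which is more conservative, has power of 82.8% at 94 and 83.3% at 95 per group, still above 80%.

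**The case against.** **All randomized patients are analysed.** The section on statistical methods includes every randomized patient in the intention-to-treat analysis. Randomization follows confirmation of resectability, and the primary endpoint is read from drain fluid from day 3 onward, so few outcomes may be lost. If all 223 are randomized and have an outcome, there is no shortfall. That is true, but the 15% allowance would then serve no purpose. The plan itself sizes for that loss and foresees exclusions after randomization. If the 15% was meant for patients lost between consent and randomization, the arithmetic is the same. The article does not define dropout, so the shortfall is conditional on the plan's own assumption.

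**The trial still has its 80% power.** A reader might infer from the shortfall that 80% power is not delivered. The document does not support that as a general statement. Under the one-sided 5% test that the section names, about 95 per group gives about 87% power. Only under a two-sided 5% test does power fall to about 79%. The two-sided reading has some support: the alternative hypothesis is worded as a difference in either direction, and 97 per group is close to a two-sided calculation (95.3 unpooled, 96.7 arcsine) and not to a one-sided one (75 to 78 by the same kinds of method). That mismatch is a separate point, and this one should not borrow weight from it.

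**The effect is negligible.** Four to five patients and about one power point are small beside the uncertainty in the assumed rates: the section says that no pilot data compare these drains, and the suction rate is simply half of 35%. This stands, and it settles the severity.

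**Conclusion.** The stated figures are inconsistent. With 15% lost, 223 enrolled patients leave about 189 to 190, not 194, and 223 covers 13.0% dropout. This follows from the article's own figures, provided that the 15% is a fraction of those enrolled and that lost patients are not replaced.

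That the figure came from 194 × 1.15 is very likely but remains an inference. The document does not support the conclusion that the trial is underpowered: power after dropout is about 87% for the test as written and about 79% for a two-sided test, about one point or less below its value at 97 per group in either case. The severity is minor. It is a wrong figure that is easily put right, with no bearing on the analysis or the error rate.

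**What to change.** Restate the enrolment sentence in one of two ways:
- enrolment of 223 allows for about 13% dropout while keeping 97 per group; or
- enrolment of 223 with 15% dropout leaves about 189 patients, 94 to 95 per group.

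Under the second wording, restate the power for the test that will actually be used (about 87% one-sided, about 79% two-sided, on the assumed rates). A few words on what counts as dropout would make either wording unambiguous.

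The cost is one sentence. No added recruitment is required. If the sponsor prefers to keep both 97 per group and the 15% allowance, the target becomes 230, seven more patients.
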